## 4.7 Safety

All safety analyses will be based on the ITT population. If the SAF population differs from the ITT population then only AE information will additionally be displayed for the SAF.

The analysis of safety will study the following primary endpoints:

1. All adverse events (AEs) and serious AEs (SAEs) collected from beginning of surgery to postoperative day 28.

|                           |                 |             |               |
|---------------------------|-----------------|-------------|---------------|
| Statistical Analysis Plan | Version 2.0     |             | Page 15 of 19 |
| Sponsor                   | [name] | Protocol No | FARES         |

- a. SAEs collected individually and as a composite (death, myocardial infarction, stroke, acute liver injury, acute kidney injury and thromboembolic events).
- b. Transfusion-Related Acute Lung Injury (TRALI) and Transfusion-Associated Circulatory Overload (TACO)

#### 4.7.1 Adverse events

Adverse events (AEs) will be coded according to the Medical Dictionary for Regulatory Activities (MedDRA). Coding will be agreed upon with the Sponsor before database lock (cf. DMP).

All adverse events recorded for patients in the SAF will be listed in the appendix of the study report differentiating by treatment emergent and non-treatment emergent events.

Only Treatment-emergent adverse events (TEAE) will be analyzed, i.e. all new and worsening pre-existing adverse events occurring after first IMP administration up to postoperative day 28. It is assumed that for each increase in intensity of an AE a new entry of the AE will be recorded by the investigator; hence such cases will be analyzed like different phases of the same AE.

A descriptive analysis will be performed. This analysis comprises the following set of tables separated by treatment group:

- Global incidence
- Incidences by primary system organ classes (SOC) and incidences of PT within primary SOC sorted according to the Internationally Agreed Order

Global incidences of primary system organ classes (SOC) and preferred terms (PT) will be calculated for

- All TEAE irrespective of the causality assessment
- TEAE by relationship (likely probable and possible related)
- TEAEs by worst severity
- Serious TEAEs

Multiple counts within a PT or SOC (repeated or different included terms or changes in descriptors) will be counted only once for the calculation of incidences.

A listing of 'special cases' containing subject identification, age, sex, AE descriptors, start and end of treatment will be prepared for the following types of TAEs:

- Fatal Serious adverse events (SAE)
- Adverse events which led to discontinuation
- Myocardial infraction
- Stroke
- Acute liver injury
- Acute kidney injury

|                           |                 |             |               |
|---------------------------|-----------------|-------------|---------------|
| Statistical Analysis Plan | Version 2.0     |             | Page 16 of 19 |
| Sponsor                   | [name] | Protocol No | FARES         |

- Thromboembolic events (according to MeDDRA SMQ)
- Transfusion-Related Acute Lung Injury (TRALI)
- Transfusion-Associated Circulatory Overload (TACO)

The number of patients who died will be summarized. A possible difference between treatment groups will be estimated by the risk ratio with 95% confidence interval. Kaplan-Meier estimates for the time to death distribution will be calculated and graphically presented.

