### **Causality of AEs**

All AEs will be assessed by a blinded Investigator as to whether they can be explained by the patient's underlying condition or surgical course. If they are not explainable, then the Investigator will make a determination of the relationship of the AE with the IMP as follows:

**Probable:** reports including good reasons and sufficient documentation to assume a causal relationship, in the sense of plausible, conceivable, likely, but not necessarily highly probable. A reaction that follows a reasonable temporal sequence from administration of the IMP; or that follows a known or expected response pattern to the suspected medicine; or that is confirmed by stopping or reducing the dosage of the medicine and that could not reasonably be explained by known characteristics of the patient's clinical state.

**Possible:** reports containing sufficient information to accept the possibility of a causal relationship, in the sense of not impossible and not unlikely, although the connection is uncertain or doubtful, for example because of missing data or insufficient evidence. A reaction that follows a reasonable temporal sequence from administration of the IMP; that follows a known or expected response pattern to the suspected medicine; but that could readily have been produced by a number of other factors.

**Unlikely:** reports not following a reasonable temporal sequence from IMP administration. An event which may have been produced by the patient's clinical state or by environmental factors or other therapies administered.

**Not related (unrelated):** events for which sufficient information exists to conclude that the etiology is unrelated to the IMP.

**Unclassified:** reports which for one reason or another are not yet assessable, e.g., because of outstanding information (can only be a temporary assessment).

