#### **Adverse events, including thromboembolic and other events of special interest**

AEs will be coded according to the latest Medical Dictionary for Regulatory Activities (MedDRA) version as specified in the Data Management Plan. The analysis will focus on treatment emergent adverse events (TEAEs), i.e., AEs that started or worsened after start of infusion with IMP.

All TEAEs, related TEAEs (i.e., AEs unlikely, probably or possibly related to the IMP), and serious TEAEs will be summarized and tabulated according to primary system organ class and preferred term. TEAEs leading to death and TEAEs resulting in withdrawal from the study will be tabulated using frequency tables if a reasonable number of events of this type are observed.

Analogous frequency tables for thromboembolic events (TEEs, identified using MedDRA SMQs), composite events, TRALI and TACO will be provided separately.

Patient listings will be provided for patients with SAEs, TEEs, AEs leading to withdrawal from the study, and AEs leading to death. Listings for non-treatment emergent adverse events, e.g. for patients enrolled but not randomized will be provided separately.

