## 15 APPENDICES

### 15.1 AE and SAE Flow Chart for Assessment and Reporting

[figure not shown]

\*1 **Serious AE (SAE)** is any untoward medical occurrence that at any dose: results in death, is life-threatening, requires hospitalization or prolongation of existing hospitalization, results in persistent or significant disability/incapacity, is another important medical event.

\*2 **eCRFs Case Report Forms Adverse Events** – Serious Adverse Events Report Form and **Concomitant Medications** Form for each adverse event

**Red legend** refer to the two conditions of expedited reporting (1) the event is serious and (2) Causality=unlikely, possible, probable, or unclassified to IMP

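### SAP 4.7.1 tabulates TEAEs by relationship using a causality grade, 'likely', that the protocol does not define, and as written omits 'unlikely', which the protocol counts as related

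*Combined protocol and SAP*

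**What the plan says.** Protocol 7.4.2 (Causality of AEs) defines five grades:

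- **Probable**: good reasons to assume causation, "in the sense of plausible, conceivable, likely, but not necessarily highly probable".
- **Possible**: "reports containing sufficient information to accept the possibility of a causal relationship".
- **Unlikely**: "reports not following a reasonable temporal sequence from IMP administration".
- **Not related**: "events for which sufficient information exists to conclude that the etiology is unrelated to the IMP".
- A fifth, holding grade, **Unclassified**, for events that cannot be judged so far; this grade is meant to be temporary.

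Protocol 9.2.1 says which of these enter the related-event table: "related TEAEs (i.e., AEs unlikely, probably or possibly related to the IMP".

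SAP 4.7.1 lists the incidence tables to be produced. Besides all TEAEs, TEAEs by worst severity and serious TEAEs, it names "TEAE by relationship (likely probable and possible related".

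SAP 2.2 states that the analysis does not depart from the protocol's statistical methods and mentions only added time windows. The derived-variable table in SAP 6.1 contains no definition of a related event.

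**The concern.** A tabulation rule has to use values that exist in the data. An investigator following protocol 7.4.2 cannot record 'likely', because the word occurs there only as a descriptor inside the definition of Probable. Meanwhile Unlikely, a grade the protocol explicitly counts as related, is missing from the SAP's list. A programmer who filters on the SAP text would find no records for one of the named values and would drop Unlikely without any error being raised.

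At stake is whether the related-TEAE table means what the protocol says it means. Protocol 1.2 gives the detection of early safety issues as one use of the pilot's safety data. Under 7.4.2 a relationship to the product is graded only for events not explained by the patient's condition or surgical course. With about 50 evaluable patients per arm (protocol 9.1), the table may be sparse, so including or excluding a whole grade could visibly change it.

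**Working it through.** No figure is stated in the plan for this point and no formula applies. The check compares sets of categories.

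| Grade (protocol 7.4.2) | Protocol 9.2.1, related | SAP 4.7.1, literal | SAP if 'likely' is a slip for 'unlikely' | SAP if 'likely probable' means Probable |
|---|---|---|---|---|
| Probable | in | in | in | in |
| Possible | in | in | in | in |
| Unlikely | in | **out** | in | **out** |
| Not related | out | out | out | out |
| Unclassified | not named | not named | not named | not named |
| 'Likely' (not on the scale) | – | named, matches nothing | – | – |

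1. Protocol set = {Probable, Possible, Unlikely}.
2. SAP set read literally = {'likely', Probable, Possible}. Mapped to the defined scale it is {Probable, Possible}.
3. Difference = {Unlikely}, the whole grade.
4. Effect on counts. SAP 4.7.1 counts a patient once within a preferred term or system organ class. A patient therefore leaves a given row only if none of their TEAEs in that row was graded Probable or Possible and at least one was graded Unlikely. The shortfall in a row is the number of such patients. It can be anything from zero to the whole row, and the documents give no counts by grade that would narrow this.
5. Is 'unlikely' in protocol 9.2.1 itself an error? The rest of the protocol suggests not. The adverse drug reaction definition in 7.4.2 takes in any event whose relationship to the product cannot be excluded. The expedited-reporting note in Appendix 15.1 also includes the grade: "Causality=unlikely, possible, probable, or unclassified to IMP". The inclusive rule fits its surroundings, and the SAP line is the one that differs.
6. Does anything else in the SAP settle the reading? SAP 6.1 does not define relatedness. SAP 2.2 does not list a change.

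**The case against.** The strongest reply is that this is a lost prefix. Protocol 9.2.1 lists three terms (unlikely, probable, possible), and the SAP lists three in the same order with only the first altered. SAP 4.7.1 has other slips, such as a misspelt infarction and a missing comma in this very line. SAP 2.2 declares no deviation, and SAP section 5 says the trial statistician checked consistency with the protocol. On that view the intended table already matches the protocol.

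This is plausible, and it means a reader should not infer that the final table is bound to depart from the protocol. It does not make the line usable: the competing reading, 'likely probable' as one term, gives a different table, and nothing in the SAP chooses between them.

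Secondly, 'by relationship' might mean a breakdown by grade rather than one pooled related count. That is possible too, but a breakdown needs the correct grade names just as much.

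Other stronger readings are tempting and not supported:

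- *That a main safety result is compromised.* SAP 4.7 names the primary safety endpoints as all AEs and SAEs, the SAE composite, and TRALI and TACO. Relatedness is not among them, and SAP 4.7.1 calls the AE analysis descriptive. Nor is the product new: protocol 1.3 describes it as approved in Canada and within the standard of care.
- *That the table contradicts expedited reporting.* Appendix 15.1 sets a trigger for serious events only, so it would differ from a table of all TEAEs anyway. It also includes unclassified events, which protocol 9.2.1 does not name.
- *That safety information is lost.* All TEAEs are tabulated regardless of causality, all AEs in the safety population are listed, and deaths, thromboembolic events and the other special cases have their own listing.

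**Conclusion.** The inconsistency is real, and the SAP line is wrong as written: it names a grade that does not exist and omits one that protocol 9.2.1 requires, with no deviation declared. Read literally, or with 'likely probable' taken as Probable, the table excludes all Unlikely events. If 'likely' was meant as 'unlikely', the intended set agrees with the protocol and only the text needs correcting.

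The effect is confined to one descriptive safety table. No efficacy analysis, sample size, all-TEAE table or serious-TEAE table changes. Its numerical size cannot be derived from the documents, and any percentage reduction would be an unsupported assumption. The conclusion rests on taking the five grades in protocol 7.4.2 as those actually recorded. It is worth correcting because the ambiguity lies in an operative rule and the correction is almost free.

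**What to change.** In SAP 4.7.1, replace the phrase with the protocol's category names: related TEAEs are those graded probable, possible or unlikely, as in protocol 9.2.1. Remove 'likely'. If the sponsor intends the narrower set of probable and possible, say so and give the reason in SAP 2.2.

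Show any events still unclassified at database lock separately. Counting them as related would go beyond protocol 9.2.1, which does not mention them. A further row restricted to probable and possible events is optional.

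The cost is one SAP sentence and, if unclassified events remain, one extra row. SAP 2.1 has the SAP finalised before any unblinded analysis, so the change belongs before that point. It needs no new data.

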#### 4.7.2 Laboratory variables

In case of derived items in the database (e.g. after transformation to standard units, see DMP), only the derived items will be analyzed. Results of all individual lab tests will be listed in original and standard units in appendix 16.2 to the clinical trial report.

The following laboratory parameter will be analyzed (as available from local labs):

|                     |                                                                                        |
|---------------------|----------------------------------------------------------------------------------------|
| Coagulation profile | PT, PTT, INR, fibrinogen activity via Clauss assay,
ROTEM EXTEM CT, ROTEM EXTEM MCF |
| Hematology          | Standard panel as per local lab                                                        |
| Clinical chemistry  | Standard panel as per local lab                                                        |
| Safety labs         | Troponin, ALT/ALP, Bilirubin, Creatinine                                               |

All laboratory values will be classified as normal or abnormal according to the laboratories' reference ranges and indicated as clinically significant or not clinically significant by the investigator on specified ranges. The following approaches will be taken for each laboratory parameter for the statistical analysis:

Quantitative data will be examined for trends using descriptive analysis (number of patients, number of missing values, mean, SD, median, quartiles, minimum, maximum) of actual values at each scheduled time point and changes from baseline to each scheduled time point. In addition mean concentration vs. time profiles (including standard deviations) will be plotted by treatment to illustrate any time trends.

Qualitative data based on reference ranges will be described according to the categories (i.e., low, normal, high).

Shift tables illustrating changes with respect to the laboratories' reference ranges between baseline and a defined scheduled time point.

Patient listings will be provided showing individual lab abnormalities.

#### 4.8 Additional safety variables

The following additional safety variables will be summarized in tables separated by treatment group and the treatment differences be explored (exploratory tests and two-sided 95% confidence intervals):

1. Duration of mechanical ventilation up to postoperative day 28
2. Duration of intensive care unit (ICU) stay up to postoperative day 28

|                           |                 |             |               |
|---------------------------|-----------------|-------------|---------------|
| Statistical Analysis Plan | Version 2.0     |             | Page 17 of 19 |
| Sponsor                   | [name] | Protocol No | FARES         |

3. Duration of hospitalization up to postoperative day 28
4. Compliance of transfusion practice with the study's hemostatic algorithm. This will include comparison of lowest hemoglobin concentration
  - during the first 24 hours after the start of surgery,
  - *during the first 24 hours after end of CPB,*
  - *during the first 24 hours after randomization,*
  - *during the first 24 hours after the start of IMP*

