###### *Exploratory Endpoints:*

1. Number of partial or full IMP doses of PCC and FP administered during the first 24 hours after the start of surgery.
2. Incidence of major bleeding, using the validated e-CABG and universal definition of perioperative bleeding (UDPB) in cardiac surgery (1, 72) scores and their individual components during the first 24 hours after start of surgery, as well as a modified version of the UDPB not including PCC and FP requirements.
3. Amount of allogeneic blood products (for each type of product and cumulatively) from start of surgery to postoperative day (POD)-7.
4. Number of patients who do not receive any RBC transfusions or any allogeneic blood transfusions from start of surgery to POD-7.
5. Number of patients receiving recombinant activated factor VII (rFVIIa) during the first 24 hours after the start of surgery
6. Number of patients receiving fibrinogen concentrate during the first 24 hours after the start of surgery.
7. Change in coagulation parameters (INR, ROTEM [EXTEM CT and MCF] and fibrinogen levels) within 75 minutes before and after IMP administration, where performed as part of standard of care.
8. Time elapsed from first IMP administration to time leaving the operating room.

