### 3.1.2 Safety Endpoints

All AEs and SAEs will be collected from beginning of surgery (defined as entry into OR) to POD-28.

SAEs will be collected individually and as a composite (death, myocardial infarction, stroke, acute liver injury, acute kidney injury and thromboembolic events).

Incidence of all transfusion reactions, including transfusion-associated circulatory overload (TACO) and transfusion-related acute lung injury (TRALI) as per the International Society of Blood Transfusion (ISBT) (16) imputability of 'possible' or higher will be compared.

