### 3.1.3 Additional Endpoints

The following additional endpoints will be collected:

1. Duration of mechanical ventilation (measured as duration of ventilation and ventilator-free days) up to POD-28.
2. Duration of intensive care unit (ICU) stay up to POD-28.
3. Duration of hospitalization up to POD-28.
4. Mortality up to POD-28.
5. Compliance of transfusion practice with the study's hemostatic algorithm based on review of patient charts by 2 blinded adjudicators. This will include comparison of lowest hemoglobin concentration during the first 24 hours after the start of surgery.

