### 2.2 Deviations from the trial protocol with regard to statistical analyses

Overall, there were no deviations from the statistical methods stated in the protocol. However, to closer study attributable efficacy and safety results, additional exploratory analyses have been added, focusing explicitly on additional time windows. The additional time windows for these exploratory analyses are identified with italic font in section 5 below.

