#### 4.6 Efficacy

The primary population for the analysis of the efficacy of the IMPs will be the ITT. The primary efficacy endpoints will also be analyzed for the PP population.

The analysis of efficacy will focus on the following primary endpoints:

P1. Treatment response, defined as effective if no additional hemostatic intervention (such as administration of hemostatic agents including a second dose of IMP, platelet transfusion, or surgical re-exploration) in the time windows

- from 60 minutes to 4 and 24 hours after initiation of the first dose of IMP,
- *from initiation of the first dose of IMP to 4 and 24 hours.*

Otherwise, treatment response will be considered as not effective, see section 6.1. If the dose of IMP is repeated within less than 60 minutes, treatment response to the IMP will be assessed for the time frames after the second IMP dose only.

P2. Amount of allogeneic blood products (for each type of product and cumulatively) administered

- during the first 24 hours after the start of surgery,
- *during the first 24 hours after the end of CPB,*
- *during the first 24 hours after randomization,*
- *during the first 24 hours after the start of first IMP dose.*

P3. Number of patients who do not receive any allogeneic blood product (in total and for each type separately)

- during the first 24 hours after the start of surgery,
- *during the first 24 hours after the end of CPB,*
- *during the first 24 hours after randomization,*
- *during the first 24 hours after the start of first IMP dose.*

In addition the following efficacy endpoints will be explored:

S1. Number of partial or full IMP doses of PCC and FP administered

- during the first 24 hours after the start of surgery.
- *during the first 24 hours after the end of CPB,*
- *during the first 24 hours after randomization,*
- *during the first 24 hours after the start of first IMP dose.*

|                           |                 |             |               |
|---------------------------|-----------------|-------------|---------------|
| Statistical Analysis Plan | Version 2.0     |             | Page 13 of 19 |
| Sponsor                   | [name] | Protocol No | FARES         |

S2. Incidence of major bleeding, using the universal definition of perioperative bleeding (UDPB) in cardiac surgery scores and their individual components

- during the first 24 hours after start of surgery,
- *during the first 24 hours after the end of CPB,*

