### 5 QUALITY CONTROL

The SAP was reviewed by the Trial Statistician (TS) before signature. Particularly the TS has checked the consistency of the described methods and outputs with the actual version of the study protocol. In addition, a sponsor representative has reviewed the SAP before final approval.

Log files of all SAS® programs used in the analysis will be checked for errors, warnings and suspicious notes by the statistical programmer. All findings will be either eliminated or commented upon. The final version of each program will be stored along with its log file in the electronic archive.

All programs will be validated by the program author or an independent statistical programmer depending on the requested validation level selected in the List of TLFs.

The agreement of the program outputs with the SAP, their consistency and plausibility will be checked by the TS. Moreover, the TS will review the outputs regarding completeness, readability and comprehensibility.

The described process is associated with the 'normal' level of program validation. Additional levels of quality control can be specified in the List of TLFs (see Appendix, 1) for individual outputs.

|                           |                 |             |               |
|---------------------------|-----------------|-------------|---------------|
| Statistical Analysis Plan | Version 2.0     |             | Page 18 of 19 |
| Sponsor                   | [name] | Protocol No | FARES         |

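### The SAP drops ventilator-free days and the e-CABG bleeding grade without saying so, and compares ventilation, ICU and hospital durations with no rule for patients who die

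*Combined protocol and SAP*

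**What the plan says.** **Ventilation.** Protocol 3.1.3, like the Study Outline, lists "Duration of mechanical ventilation (measured as duration of ventilation and ventilator-free days) up to POD-28". SAP 4.8 lists "Duration of mechanical ventilation up to postoperative day 28". Ventilator-free days appear nowhere in the SAP.

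**Major bleeding.** Protocol 3.1.1 has "Incidence of major bleeding, using the validated e-CABG and universal definition of perioperative bleeding (UDPB) in cardiac surgery", plus a modified UDPB that leaves out PCC and FP. SAP 4.6 has "S2. Incidence of major bleeding, using the universal definition of perioperative bleeding (UDPB) in cardiac surgery scores and their individual components", plus the same modified UDPB. In the SAP, e-CABG survives only in the list of abbreviations.

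**Disclosure.** SAP 2.2 states: "Overall, there were no deviations from the statistical methods stated in the protocol". The only differences it declares are added time windows. The revision history for version 2.0 lists four changes, none of them these omissions. SAP section 5 adds: "Particularly the TS has checked the consistency of the described methods and outputs with the actual version of the study protocol".

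**Durations.** SAP 4.8 plans summaries by arm, exploratory tests of unnamed type and 95% confidence intervals for ventilation, ICU and hospital duration to day 28. Neither SAP 4.8 nor SAP 6.1 defines the start, end, censoring or handling of death. SAP 4.1.2 rules out imputation. SAP 4.7.1 analyses mortality separately, by risk ratio and Kaplan-Meier.

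**Transfusion reactions.** Protocol 3.1.2 speaks of "Incidence of all transfusion reactions, including transfusion-associated circulatory overload (TACO) and transfusion-related acute lung injury (TRALI", at ISBT imputability of possible or higher. The Study Outline (same threshold) and protocol 9.2.1 name only TRALI and TACO. SAP 4.7 also names only those two, without the threshold.

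**The concern.** Followed as written, the SAP does not produce two measures that the protocol promises, and a reader of its deviations section would not learn this. One of them, ventilator-free days, is the only protocol measure that can combine death with time on the ventilator. What is left for ventilation, ICU and hospital stay is a between-arm comparison of raw durations, in which death competes with discharge and extubation. A difference in such a duration cannot be read as faster or slower recovery unless the treatment of deaths is fixed beforehand. The SAP presents these durations as safety variables, so a misread direction would matter.

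**Working it through.** **1. Endpoint by endpoint.**

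| Item | Protocol | SAP | Disclosed in SAP 2.2 or revision history? |
|---|---|---|---|
| Ventilation duration | 3.1.3 | 4.8 | kept |
| Ventilator-free days | 3.1.3 | absent | no |
| UDPB, modified UDPB | 3.1.1 | 4.6 (S2) | kept |
| e-CABG | 3.1.1, 6.1.2, 7.2.3 | abbreviation list only | no |
| 28-day mortality | 3.1.3 | 4.7.1 | kept, moved |
| All transfusion reactions | 3.1.2 only | absent | no; the Study Outline and 9.2.1 agree with the SAP |

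The plan gives no figure for these endpoints, so there is none to reproduce.

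**2. Effect of one death on an arm mean.** The planned evaluable number is 50 per arm (SAP 1.3). Survivor means and death times are assumptions, because the documents give none. If the duration ends at death,

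change in arm mean = (day of death − survivor mean) / 50.

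For one extra death on day 1:

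- Hospital, survivor mean 7 to 14 days: (1 − 7)/50 = −0.12 to (1 − 14)/50 = −0.26 days.
- ICU, survivor mean 2 to 6 days: (1 − 2)/50 = −0.02 to (1 − 6)/50 = −0.10 days.
- Ventilation, survivor mean 0.5 to 2 days: (1 − 0.5)/50 = +0.01 to (1 − 2)/50 = −0.02 days.
- Ventilator-free days with death scored 0: −(28 − 0.5)/50 = −0.55 to −(28 − 2)/50 = −0.52 days.

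**3. Difference between arms.** Assume 28-day mortality of 2% and 10%, identical survivors in both arms, and patients who die remaining ventilated, in ICU and in hospital until death. Assume lognormal times: ventilation with median 0.6 days (sigma 0.9), further ICU time with median 2 (0.8), further ward time with median 6 (0.5). A lognormal mean is median × exp(sigma²/2):

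- ventilation 0.6 × 1.499 = 0.90 days
- ICU 0.90 + 2 × 1.377 = 3.65 days
- hospital 3.65 + 6 × 1.133 = 10.45 days

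Then difference (higher minus lower mortality) = 0.08 × (mean day of death − survivor mean). Death times are uniform from day 0.2, so their means are 1.1, 3.6 and 14.1 days.

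| Deaths up to day | Ventilation | ICU | Hospital | Ventilator-free days, death = 0 |
|---|---|---|---|---|
| 2 | +0.02 | −0.20 | −0.75 | −2.17 |
| 7 | +0.22 | 0.00 | −0.55 | −2.17 |
| 28 | +1.06 | +0.84 | +0.29 | −2.17 |

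The last column is −0.08 × (28 − 0.90). A simulation with the same inputs, 50 per arm, durations capped at 28 days and 2,000 replicates, agreed to about 0.01 day.

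**4. Reading.** The sign of a raw duration changes where the mean day of death equals the survivor mean: here about day 10.5 for hospital, 3.7 for ICU and 0.9 for ventilation. Ventilator-free days with death scored 0 move against the arm with more deaths whatever the timing.

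**The case against.** Several stronger readings are tempting, and the documents do not support them.

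- **SAP 2.2 is false.** Its sentence is about statistical methods. Omitted endpoints are a gap in disclosure more than a literal contradiction. Protocol section 9 also leaves analysis detail to the SAP. What stands is that this is the SAP's deviations section, and section 5 extends the consistency check to outputs.
- **The SAP scores an early death as a good, short stay.** It does not; it is silent. That scoring is what follows if a stay is simply closed at death.
- **Deaths are hidden.** They are not. Mortality has its own analysis, and death is in the SAE composite. It is only not combined with the durations.
- **The distortion is large.** One can construct a case: 4 of 50 patients who would have stayed 20 ICU days die on day 2, and the mean falls by 4 × 18/50 = 1.44 days. This is one assumed scenario. If those four would have stayed 4 days, the fall is 4 × 2/50 = 0.16. If they die late in ICU, the mean can rise.
- **The SAP removed the comparison of all transfusion reactions.** Only protocol 3.1.2 promises it; the Study Outline and 9.2.1 match the SAP. This is a contradiction inside the protocol. Other reactions reported as treatment-emergent events would still appear in the SAP 4.7.1 incidence tables.
- **A Phase 3 bleeding endpoint is lost.** The protocol lists major bleeding as exploratory and does not name e-CABG as a Phase 3 candidate. UDPB is kept.

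It is also fair that the trial is a pilot without a sample-size calculation, and that the separate list of tables might add outputs. That list could not correct the SAP text.

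**Conclusion.** The point holds in limited form. Two protocol measures, ventilator-free days and e-CABG, are missing from the SAP, and nothing in it says so. This follows from the text alone and rests on no assumption.

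The lack of a death rule for the three durations is also plain from the text. Its size is not known. In the assumed 2% versus 10% case, hospital stay moves between −0.75 and +0.29 days and ICU stay between −0.20 and +0.84, according to when deaths occur. Ventilation is hardly affected by very early deaths and lengthened by late ones. These figures show direction and order of size only; they depend on the assumed mortality, survivor times and death times.

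The endpoints are additional or exploratory, and mortality is reported by arm. The correction is worth making but does not threaten the trial's main purpose. The transfusion-reaction wording is a separate matter of reconciling the protocol with itself.

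**What to change.** - **SAP 4.8:** restore ventilator-free days to POD-28 with an explicit death rule, for example death by POD-28 = 0. The protocol defines none, so this is an addition. Compare with a rank-based test, since the scores pile up at zero and near 28. Show the result beside mortality, because with short ventilation times deaths will dominate it.
- **SAP 4.8, ICU and hospital stay:** state start, end and handling of death. Either use free days under the same rule, or show raw durations descriptively by survival status.
- **SAP 4.6 (S2):** restore e-CABG, with its definition of major bleeding.
- **SAP 2.2:** list every protocol endpoint not carried through, with the reason. If either measure was dropped on purpose, this entry is the minimum.
- **Transfusion reactions:** reconcile protocol 3.1.2 with the Study Outline and 9.2.1, and carry the ISBT threshold into SAP 4.7.

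The cost is SAP wording and a few tables. Protocol 6.1.2 to 6.1.4 already collect extubation time, ICU and hospital stay, 28-day outcome and the e-CABG and UDPB components, and the Kaplan-Meier analysis already needs the time of death. The death rule should be fixed before unblinding; if that has passed, label it as added afterwards.
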